### Interventions

Patients will receive either 25 mg exogenous melatonin (intervention group) or matching placebo (control group) in an orally administered pill. Regarding the active substance each pill will contain 12.5 mg melatonin, and the placebo pill will be comparable to study medication except for the active substance. The medication will be packaged in blister packs consisting of 30 pills in each, and a total of seven blister packages will be packaged in a cardboard box (total of 210 pills). Patients will be instructed to take two pills (daily dose of 25 mg active substance) approximately 1 h before bedtime during the entire length of the study (12 weeks). Medicine compliance will be investigated at weeks 2 and 12 at clinical visits. All study medication will be produced by PharmaNord Aps. (Vejle, Denmark) in accordance with Good Manufacturing Procedure (GMP). The study medication will be shipped to the Region Zealand Hospital Pharmacy which will handle the randomization process.

If a participant withdraws their consent, they will leave the study. In the unlikely event that a female participant should become pregnant despite using reliable birth control, she will leave the study. Patients who have a recurrence of ACS during the study will be withdrawn from the study. In case of severe medical emergency (e.g., stroke or severe sepsis) requiring emergency surgery, stay in an intensive care unit, or more than 1 week of hospitalization will result in exclusion from the study. Diagnosis of a cancer during the study period will also result in withdrawal from the study. No further data will be collected from patients after leaving. However, previously collected data will be part of the final data analysis. No change in dose of study medication will be possible during the trial.

A medicine compliance of a minimum of 75% (pill count) at the clinical visits at weeks 2 and 12 are required. If the patients do not comply with these demands at either visit, they will be excluded from the study. Exclusion from the study entails stopping the study medication, and patient’s data will not be part of a per-protocol analysis. In case of medicine compliance at the first clinical visit, the data collected until this point will be part of a per-protocol analysis.

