If a patient is diagnosed with a moderate-to-severe depression on the MDI during the study, they will be referred to a psychiatrist in training attached to the study (who is blinded to the allocated treatment). The psychiatrist in training will perform a structured clinical interview (Hamilton Depression Scale) with the purpose of diagnosing depression and its severity according to the *International Classification of Diseases, version 10* (ICD-10) criteria. Patients with a moderate-or-severe depressive episode according to the Hamilton Depression Scale and clinical assessment will be withdrawn from the study and offered open treatment for depression via the patient’s general practitioner (GP). All outcome data collected until the eventual termination in the study will be part of the final analysis. If the patient is diagnosed with a mild depression on the MDI, they will be allowed to continue in the study. The patient will be monitored using the MDI and phone calls according to the study protocol. In case of symptom progression on the MDI into moderate to severe depression, the participant will be referred to the psychiatrist in training as described above.

Patients will be contacted by phone seven times (every 2 weeks) during the trial to assure compliance and to promote their retention during follow-up. The patients will be reminded to fill in the relevant study questionnaires, reminded to take study medication, and monitored for occurrence of any adverse reactions, or changes in other medication since last contact with study investigators.

The participants are allowed to participate in all offered concomitant care at their regional cardiology department (e.g., cardiac rehabilitation). Startup of any medical antidepressant treatment in the trial period is prohibited and will lead to exclusion from the trial.

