### Statistics

Descriptive data on baseline characteristics and results will be presented as mean, SD, and *n* and presented in tabular form. Distribution of data will be tested by using data plots and by visually assessing data, and potentially continuous variables will be visualized in a matrix plot. Appropriate statistical tests will be used accordingly depending on distribution. Log transformation will be applied if applicable.

Our null hypothesis is that there will be no difference in the number of participants developing depressive symptoms (defined as a MDI score ≥21) throughout the study period between the melatonin and the placebo group. The hypothesis is assessed using Fisher’s exact test and/or the chi-squared test.

For the primary outcome analysis, a linear mixed model will be applied. The effect of age, gender, comorbidity and cardiac risk factors will be assessed by marginal analysis. Results will be assessed through an analysis on complete data generated using multiple imputation.

As a secondary analysis, the cumulative incidence of depressive symptoms will be plotted for the two groups and compared using the log-rank test assuming the absence of competing risks. Incidence of depressive symptoms (MDI score ≥21) will be analyzed using the Cox proportional hazards regression, including analysis of effects of age, gender, comorbidity and cardiac risk factors at baseline.

A principle analysis will be performed according to the intention-to-treat principle (ITT). The intention-to-treat population is defined as every patient randomized into the trial. A per-protocol analysis will also be performed. A per-protocol participant is defined as a patient who has taken medication in accordance with the protocol (at least 75%) for the first 14 days (until the follow-up visit). In cases of noncompliance with the medication before the follow-up visit (i.e., exclusion from the study), another patient will be enrolled to make up for the lost patient. Finally, a standard sensitivity analysis will be performed on the per-protocol patient population.

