For secondary/exploratory outcomes, intergroup comparison for anxiety and depression (HADS) will be made at baseline, 2 and 12 weeks. The data originating from the actigraphy measurement will be presented as sleep and circadian outcomes. The sleep outcomes will be divided into units of 3 days as recommended [59], and descriptive data will be presented for the entire 2-week measuring period. Sleep diary and VAS measured each day simultaneously with actigraphy will be termed short-term sleep/VAS outcomes. Sleep diary and VAS measured afterwards every 2 weeks will be termed long-term sleep/VAS outcomes. Intergroup comparisons of PSQI data will be made at baseline, 4, 8 and 12 weeks. For all continuous data, intergroup comparisons will be done using an unpaired Student *t* test or Mann-Whitney’s test depending on distribution of data. For analysis of the correlation between circadian genotype, depressive symptoms and sleep, a logistic regression analysis will be used.

A *P* value < 0.05 will be considered statistically significant. For exploratory outcomes all analysis will be presented and no statistical correction for multiple testing will be applied [60]. No interim analysis is planned for the study. A priori, no subgroup analysis is planned [61]. The statistical analysis plan has been consulted with an external independent statistician. The analysis of data will, upon study completion, be handled and performed by the first author, and the process will be aided by the external study statistician. An appropriate statistical software package will be applied for the statistical analysis.

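### HADS and PSQI are tested between arms visit by visit without using their baseline scores; week 12 also leaves out patients withdrawn for depression, which would dilute a real effect if withdrawal differs by arm

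*Protocol article*

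**What the plan says.** The protocol article's Statistics section sets the comparison times for the two main questionnaires outside the primary outcome. For HADS, "intergroup comparison for anxiety and depression (HADS) will be made at baseline, 2 and 12 weeks". For the sleep index, "Intergroup comparisons of PSQI data will be made at baseline, 4, 8 and 12 weeks". The test is fixed as well: "For all continuous data, intergroup comparisons will be done using an unpaired Student" t test, or a Mann-Whitney test if the distribution calls for it. No baseline covariate or repeated-measures model is given for these scores.

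The Interventions section decides who is still there to be scored. "Patients with a moderate-or-severe depressive episode according to the Hamilton Depression Scale and clinical assessment will be withdrawn from the study". Milder cases stay: "If the patient is diagnosed with a mild depression on the MDI, they will be allowed to continue in the study". A second route out is given as "Startup of any medical antidepressant treatment in the trial period is prohibited and will lead to exclusion from the trial". After either, "No further data will be collected from patients after leaving", and the Data collection section likewise stops collection once study medication is stopped.

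A linear mixed model and multiple imputation do appear in the Statistics section, but in the paragraph on the primary outcome. The paragraph on HADS and PSQI does not extend them.

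**The concern.** Three features of the stated analysis deserve attention.

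- **Baseline tests.** Any baseline difference between randomised arms is due to chance, so a test there answers no question.
- **Unused baseline scores.** Both scales are measured at baseline and again later, yet the follow-up comparison ignores the first measurement. That gives up precision that costs nothing to obtain.
- **Selected remainder at week 12.** HADS measures anxiety and depression. Withdrawal for confirmed moderate or severe depression will tend to remove high scorers. If one arm loses more of them, a comparison of those remaining no longer compares the randomised groups.

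The Aim section names anxiety, sleep and circadian effects as the secondary aims. A null week-12 result on these scales could then reflect a weak test on a selected remainder rather than the absence of an effect.

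**Working it through.** **The plan's own figure.** The Sample size section gives 31% v 15.5%, two-sided 5%, power 0.80, and 116 per group. With the pooled-variance formula and a mean proportion of 0.2325:

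n = [1.96·√(2·0.2325·0.7675) + 0.84·√(0.31·0.69 + 0.155·0.845)]² / 0.155² = 115.4, rounded up to 116.

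The figure reproduces. It concerns the binary MDI outcome; the article gives no SD, correlation or target difference for HADS or PSQI. What follows is therefore in SD units, with assumptions marked.

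**Detectable difference with the stated test.** With 120 per arm and no losses: (1.96 + 0.84)·√(2/120) = 0.36 SD at 80% power.

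**Gain from using baseline.** Adjustment leaves a fraction 1 − r² of the variance, where r is the correlation between baseline and follow-up (assumed). The equivalent increase in patients is 1/(1 − r²) − 1.

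| r (assumed) | Variance removed | Equivalent extra patients | Power at 0.36 SD | Power at 0.30 SD |
|---|---|---|---|---|
| 0 (stated test) | 0% | 0% | 0.80 | 0.64 |
| 0.3 | 9% | 10% | 0.84 | 0.68 |
| 0.5 | 25% | 33% | 0.90 | 0.77 |
| 0.7 | 49% | 96% | 0.975 | 0.90 |

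**Withdrawal, simple bound.** Removing the worst fraction q of a standard normal lowers the mean of the rest by φ(z)/(1 − q). For q = 10% this is 0.195 SD and for q = 5% it is 0.109 SD. If placebo loses 10% and melatonin 5% (assumed rates), the difference between arms shrinks by 0.195 − 0.109 = 0.086 SD. That requires the withdrawn patients to be exactly the worst scorers on the scale analysed. If withdrawal correlates 0.6 with the week-12 score (assumed), the shrinkage is 0.6 × 0.086 = 0.052 SD.

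**Withdrawal, simulation.** A normal liability to depression has correlation 0.5 to 0.9 with the week-12 score. Everyone above a threshold leaves before week 12, and melatonin shifts liability and score by the same number of SDs.

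| Withdrawn, placebo v melatonin (assumed) | Share of true week-12 difference still seen |
|---|---|
| 10% v 5% | 79% to 88% |
| 20% v 10% | 68% to 82% |
| 31% v 15.5% | 60% to 78% |
| 20% v 20%, no effect | between-arm bias about zero |

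The third row takes the plan's rates for MDI ≥21. It is an upper bound, because mild cases stay and withdrawal needs clinical confirmation. In the last row both arm means fall by about 0.25 SD (at correlation 0.7), but by the same amount.

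**How far baseline adjustment repairs this.** At 10% v 5%, with a baseline correlation of 0.5 and liability-to-score correlations of 0.6 to 0.9, the share retained rises from about 79–86% unadjusted to about 84–91% adjusted. Imputation that also uses the MDI recovers about 100%, provided withdrawal depends only on the MDI.

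**The case against.** The outcomes table lists these outcomes as exploratory, and the plan promises to present all analyses without multiplicity correction. Under randomisation an unadjusted two-sample test is valid, only less efficient, and a baseline test is uninformative but biases nothing. That stands, and it limits the weight of the point. It does not remove it, because the article fixes the test rather than leaving it open.

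The gain depends on a correlation that the documents do not give. At 0.3 it is modest, so the whole range has to be shown.

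A reader might infer that the week-12 comparisons are simply biased towards no effect. The documents do not support that. The bias arises only if withdrawal differs by arm; only confirmed moderate or severe episodes and antidepressant starts lead out by these routes; the 10% and 5% rates appear nowhere in the article; and the trigger is the MDI and the Hamilton scale, not HADS or PSQI. The earlier comparisons (HADS at week 2, PSQI at week 4) are less exposed.

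It is also fair to say that a baseline covariate alone does not cure the selection. A patient withdrawn at week 6, say, has no scheduled HADS value that reflects the deterioration. The fix therefore needs imputation that uses the MDI.

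An unseen analysis plan may extend imputation to these scores. To adjust for baseline, however, it would have to depart from the test stated here.

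**Conclusion.** The point holds for HADS and PSQI, at moderate weight. The baseline tests serve no purpose, and the follow-up tests give up 9% to 49% of the variance over assumed correlations of 0.3 to 0.7.

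The withdrawal effect is conditional. If melatonin works and placebo loses more patients to confirmed depression, the week-12 differences would probably shrink, by about 0.05 to 0.09 SD at an assumed 10% v 5%, against 0.36 SD detectable. With equal withdrawal the bias is about zero. Its actual size cannot be computed from the article.

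Two extensions are tempting and not supported. First, a reader might infer that baseline MDI is wrongly left out of the primary-outcome models. The relevant wording, "including analysis of effects of age, gender, comorbidity and cardiac risk factors at baseline", names effects to be examined and is not presented as a full covariate list, and a mixed model may already carry baseline MDI. Second, a reader might extend the criticism to VAS and the sleep diary. The visible text documents no pre-treatment VAS or diary value, and visit-by-visit comparison is explicit only for HADS and PSQI.

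The primary sample size is unaffected.

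**What to change.** 1. For HADS and PSQI, replace the visit-by-visit tests with a baseline-adjusted model: ANCOVA at each follow-up, or one mixed model with treatment, visit, treatment-by-visit and baseline score. Report the week-12 adjusted difference with its 95% CI.
2. Drop the between-arm tests at baseline and describe baseline scores by arm only.
3. Extend the multiple imputation already stated for the primary outcome to these scores, with the two-weekly MDI in the imputation model. State the assumption that, given the observed MDI and other scores, withdrawal carries no further information about the missing values. It cannot be checked, since nothing is recorded after leaving, so the result should be presented as exploratory.
4. Keep the simple comparison where no baseline value exists: actigraphy, and VAS or diary unless a pre-treatment value is recorded.

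The cost is wording and some analysis time. No new visits, measurements or patients are needed; the baseline scores and the MDI are already collected. Scores after withdrawal do not exist and are not asked for. The article reports 150 of 240 patients included, so the change can be settled before the treatment code is broken.

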### Harms and adverse events

To monitor harms and adverse events two systems will be employed in the current trial. Firstly, at each clinical visit and during each phone call the patient will be interviewed regarding possible side effects according to the summary of product characteristics which contains a list of known side effects. Furthermore, an open-ended question regarding side effects will be asked to try to detect any unexpected side effects.

Secondly, the “udvalg for klinisk undersøgelser” (UKU) manual will be used to monitor harms. The UKU has been developed for monitoring the side effects of psychotropic drugs and has been validated in several Nordic countries [62]. A self-rating version of the UKU side effect rating scale (UKU-SERS-Pat) has been developed and validated against the clinician-administered version (UKU-SERS-Clin) [63]. The UKU-SERS-Clin is time-consuming which may hinder its usage in clinical practice with the possibility of overlooking severe side effects that may be avoided. Furthermore, development of a patient-administered version may gain more information about side effects as patients and clinicians perceive them differently [63]. Overall, the intercorrelation between the patient- and clinician-administered UKU was shown to be statistically significant [63]. When working with antidepressants, the UKU-SERS paper [62] states that neurological symptoms may be omitted from the evaluation, and this will be done in the current study. In the current clinical trial, the UKU-SERS-Pat will be administered at the clinical visits and in the ambulatory setting at the point in the trial when the clinical status (MDI) is being evaluated.

### Ethics, monitoring and reporting

The study will be performed in agreement with the Helsinki II Declaration and law 593 of 2011 pertaining to the Scientific Ethics Committee System. The project is registered at www.ClinicalTrials.gov (NCT02451293) as recommended by the International Committee of Medical Journal Editors (ICMJE). The Good Clinical Practice Unit at Copenhagen University will oversee the trial and conduct monitoring visits of the trial periodically. The protocol has followed the SPIRIT guidelines (Additional file 1), and the manuscript will follow the CONSORT Statement [64]. In accordance with CONSORT guidelines, both positive, neutral and negative findings will be published [64]. In case of important modifications to the protocol (e.g., changes in eligibility criteria), trial investigators will be informed and the www.ClinicalTrials.gov registration updated. Authorship guidelines put forth by the ICMJE will be applied for all publications originating from the current trial.

## Discussion

The current manuscript describes a protocol for a primary prophylactic study targeting nondepressed patients following ACS. To the best of our knowledge, we are the first to investigate melatonin’s antidepressant, anxiolytic and hypnotic effects in this population.

The predominant focus of previous trials has been the treatment of depression in patients following ACS. A recent Danish study showed that 20% of patients following ACS have an incident depression and 67% of medical antidepressant treatment is made up of selective serotonin reuptake inhibitor (SSRIs) [65]. This is coherent with a systematic review describing the increased use of antidepressants (predominantly SSRIs) during the last three decades [66]. Awareness and treatment of depression following ACS has risen during the last decades; however, not much attention has been focused on preventive interventions.

We know of only one previous trial using a similar primary preventive strategy [67, 68], which showed an effect of prophylactic treatment with escitalopram (Cipralex) [67]. However, treating patients with a SSRI (SSRI before the onset of depression is not without risk. Treatment with SSRIs have been shown to be associated with sleep disturbances, sexual disturbances and arrhythmias [30]. Recently, specific concerns regarding the cardiotoxicity of citalopram (also escitalopram) have been raised [69]. There exists a dose-response relationship between citalopram and the prolonged QT interval syndrome which, in some cases, leads to sudden cardiac death. Furthermore, patients with a previous cardiac event (e.g., MI) constitute a high-risk population [69]. The DECARD trial [67] has, in light of this, been criticized for the unnecessary potential harm associated with SSRI treatment caused to nondepressed patients with a previous cardiac event. The premise of preventing the development of depressive symptoms in the specific population is, however, controversial. Any such intervention should, of course, have the highest degree of benefit and the lowest incidence of side effects.

Melatonin was chosen for the current trial in light of these considerations, and on the basis of positive results from a previous similar trial in women with breast cancer [37]. It should be mentioned that the study did not include the planned number of patients due to slow recruitment; however, the effect of melatonin was greater than assumed a priori [37]. Melatonin has repeatedly been shown to have sleep-improving effects in women with breast cancer [38, 70, 71]. As melatonin is widely safe and nontoxic, even when given to animals and humans in high exogenous doses over extended time periods [35, 45, 72], it would be a good candidate for a prophylactic setup. Exogenous melatonin has been investigated in multiple clinical trials and with multiple outcomes [31, 43]. Melatonin has recently been reviewed as treatment for clinical depression in both prophylactic and treatment setups [43], where no significant antidepressant effect of melatonin was shown in either setting. However, it was concluded that the included studies were heterogonous and of low quality, and that further properly dimensioned trials will be needed before any conclusion can be made. The review does not include the previously mentioned positive prophylactic melatonin trial performed in breast cancer patients [37]. Furthermore, the included trials have used a low dose of melatonin, typically under 10 mg [43] which is the dose used for treatment of insomnia in patients aged over 55 years [44]. It has been argued by Cardinali et al. that the antidepressant potential of melatonin cannot be determined before trials using equivalent doses of melatonin compared to other melatonergic agonists [30] have been performed. This would constitute trials of 25–100 mg melatonin, and taking into consideration the prophylactic setup of our trial, we chose a dose of 25 mg. In a dose-response study, a dose of 25 mg Valdoxan (agomelatine, a melatonin agonist) was found to be most effective as an antidepressant [73], and 25 mg is typically the recommended induction dose for Valdoxan in treatment of major depressive disorders. To the best of our knowledge, a similar dose-response trial does not exist for melatonin in relation to its antidepressant effect. Twenty-five milligrams is, therefore, arbitrarily chosen, but it is never-the-less the dose chosen in light of the dose-response antidepressant effects seen in melatonin agonists.

Besides the positive effect on depressive symptoms, melatonin may also be used to treat anxiety, sleep and circadian disturbances. Melatonin has been recommended as the first-line treatment of patients aged over 55 years suffering from insomnia, parasomnia and circadian rhythm sleep disorders [44]. Exogenous melatonin administered in the perioperative period has recently been reviewed [31], showing a significant anxiolytic and analgesic effect. Overall, melatonin is a relevant and safe intervention to be tested for potentially beneficial effects against depressive symptoms, anxiety and sleep and circadian disturbances in patients following ACS.

